### Inclusion and exclusion criteria

For the present study, T2DM patients, aged 30–60 years, with a diagnosis of T2DM for at least 2 years, HbA1C value greater than 7%, body mass index (BMI) between 25 and 35 kg/m^2^, who will be treated with a stabilized dose of oral anti-diabetic drugs and statins will be included in the study.

Patients will be excluded if: 1) they are pregnant or lactating; 2) have gastrointestinal disorders that interfere with the bowel function, severe hepatic, renal (dialysis), inflammatory and thyroid diseases; 3) being on insulin therapy or need insulin based on expert physician’s opinion 4) have diabetes complications including micro and macrovascular complications; 5) take warfarin, fibrates (PPAR- α ligand), TZD (PPAR- gammaligand) and anti-depressant agents; 6) adhering to a specific diet during the past 3 months; 7) have history of smoking or alcohol intake at least once a week in the past month; 8) receive (at least once a week) herbals, antioxidant, multivitamin/mineral supplements in the past 3 months; 9) they were unstable on the current dose of medications. Patients, who consume less than 90% of their intervention, will also be excluded.

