#### Study outcomes

##### Primary outcomes

The primary outcomes of this clinical trial are the changes in HbA1C, FBS, insulin, lipid profile (triglyceride, total cholesterol, HDL-cholesterol, LDL-cholesterol), oxidative stress biomarkers such as TAC, SOD, GPx, MDA, SIRT1 and irisin at the end of the study in comparison with the baseline values.

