##### Procedure

After obtaining the informed consent, both groups will be visited at the clinical research center twice: at baseline, and after 10 weeks. Subjects will be interviewed regarding their socio-demographic background at baseline. At each visit, anthropometric indices (weight, height and waist circumference) will be measured, fasting blood sample will be collected and a 24-h food recall and international physical activity questionnaire (IPAQ) will be obtained.

Height will be measured using the SECA stadiometer to the nearest 0.1 cm and weight will be measured using a SECA electronic scale to the nearest 0.1 kg. Waist circumference will be measured midway between the lowest rib and the iliac crest using a non-stretchable measuring tape to the nearest 0.1 kg. BMI will be calculated as weight (kg) divided by height squared (m^2^). Venous blood sample (10 ml) will be drawn after 12-h overnight fasting by trained nurses in seated position to measure biochemical markers. Then blood samples will be centrifuged at 3000 rpm for 10 min at 4 °C to obtain the serum and plasma and will be stored at −80 °C until biochemical analyses. Lipid profiles (TC, HDL, LDL, TG) and glucose level will bemeasured by the enzymatic colorimetric method using kits. Serum insulin will be measured using enzyme-linked immunosorbent assay (ELISA) kit. Insulin sensitivity and insulin resistance will be determined using the QUICKI and HOMA-IR equation, respectively.$$ \mathrm{QUICK}=1\kern0.5em /\kern0.5em \left(\log \left(\mathrm{fasting}\kern0.5em \mathrm{insulin}\ \upmu \mathrm{U}/\mathrm{ml}\right)\kern0.5em +\kern0.5em \log\ \left(\mathrm{fasting}\  \mathrm{glucose}\ \mathrm{mg}/\mathrm{dl}\right)\right) $$$$ \mathrm{HOMA}\hbox{-} \mathrm{IR}=\kern0.5em \left(\mathrm{FPI}\left(\mathrm{mU}/\mathrm{l}\right)\kern0.5em \times \kern0.5em \mathrm{FPG}\kern0.5em \left(\mathrm{mmol}/\mathrm{l}\right)\right)/22.5 $$

Serum TAC [28] and level of SOD and GPx in red blood cells will be measured by spectrophotometric methods using kits. Serum irisin and SIRT1 will be measured using ELISA kits.

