##### Statistical analysis

All statistical analyses will be performed using SPSS version 21 (SPSS Inc., Chicago, USA). Data will be expressed as mean ± SD for continuous variables and percentage for non-continuous variables. Normality tests will be assessed through Shapiro-Wilk tests carried out on each parameter before analysis. All outcome variables will be assessed based on intention-to-treat and per protocol analysis. Missing data will be entered using “regression imputation” method. To compare the mean differences between the two groups, the independent *t*-test and Mann–Whitney will be used for normal and non-normal data respectively, considering the normality of data. A multivariate repeated-measures regression analysis will be used to assess time effects and time-by-treatment interactions effect on all outcome variables. A *p*-value of less than 0.05 will be considered as significant.

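### A normality pre-test picks one treatment comparison and a repeated-measures model supplies another, with neither named as primary and neither adjusting for baseline

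*Protocol article*

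**What the plan says.** All of the following is in the protocol article.

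- **Pre-test** (Statistical analysis): "Normality tests will be assessed through Shapiro-Wilk tests carried out on each parameter before analysis".
- **Test chosen by it** (Statistical analysis): the group comparison is described as one of mean differences. The t-test and Mann-Whitney "will be used for normal and non-normal data respectively, considering the normality of data".
- **Second analysis, not conditional on normality** (Statistical analysis): "A multivariate repeated-measures regression analysis will be used to assess time effects and time-by-treatment interactions effect on all outcome variables".
- **Threshold for every test** (Statistical analysis): a p-"value of less than 0.05 will be considered as significant".
- **Analysis sets** (Statistical analysis): "All outcome variables will be assessed based on intention-to-treat and per protocol analysis". Neither set is given priority.
- **Outcome definition** (Primary outcomes): changes in 13 markers "at the end of the study in comparison with the baseline values".
- **Visits** (Procedure): "both groups will be visited at the clinical research center twice: at baseline, and after 10 weeks". The mid-study measurement is of diet only.

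Continuous variables are summarised as mean ± SD throughout.

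**The concern.** The plan treats non-normality as a reason not to use the t-test, then fits a repeated-measures regression to the same outcomes without mentioning normality. A skewed marker therefore ends with two treatment p-values, each eligible to be called significant, and the article does not say which is the result.

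Three things follow:

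- The observed data choose the test, so the quantity being compared can differ from one primary marker to the next.
- An outcome sent to Mann-Whitney has a p-value that does not belong to the mean ± SD printed beside it.
- Neither stated analysis conditions on the baseline value, although that value is collected for every outcome. This costs power.

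**Working it through.** **1. Inputs.** The article gives 40 per group, a 20% drop-out allowance, two outcome visits and a 0.05 threshold. It gives no SD, skewness or baseline-to-week-10 correlation, and its sample size rests on a cited TAC difference that is not shown. The 40 therefore cannot be reproduced. If 40 already includes the allowance, the evaluable number is 40 × 0.8 = 32 per arm. By the article's formula that implies a standardised difference of √(2 × (1.96 + 0.84)² / 32) ≈ 0.70. The calculations below use 32 per arm (40 where stated). Effect size, correlation and skew are assumptions.

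**2. The interaction test with two visits.** Let D be week 10 minus baseline. The time-by-treatment F statistic is

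F = (mean D in arm 1 − mean D in arm 0)² / [s²(D) × (1/n₁ + 1/n₀)] = t²,

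where t is the two-sample t statistic on change. In a simulated data set with 32 per arm, both gave p = 0.8299. If the t-test is applied to change, as the outcome definition suggests, a normal outcome gains nothing from the second analysis. If Shapiro-Wilk rejects, the plan has Mann-Whitney on change alongside what is in effect the t-test on change.

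**3. How often the two answers differ.** 8,000 simulated trials per setting, assumed correlation 0.5, lognormal data with log-SD 0.5 (moderate skew) or 1.0 (strong skew), or normal data. Among trials flagged by Shapiro-Wilk, the two p-values fall on opposite sides of 0.05 as follows:

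| Setting | Discordant |
|---|---|
| No effect | 3–5% |
| 0.5 SD effect, normal or moderate skew | 10–14% |
| 0.5 SD effect, strong skew | 21–22% |

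With strong skew and that effect, power is 48% by the pre-test route and 36% by the interaction at 32 per arm (56% and 43% at 40).

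**4. Type I error.** Each route alone stays near 5% (4.2–5.4%). If either may be claimed, the rate is 5.0–5.5% for normal, 5.9–6.2% for moderately skewed and 6.8% for strongly skewed outcomes. Two independent tests would give 1 − 0.95² = 9.75%. The article does not say outright that the t-test or Mann-Whitney uses change. If it used week-10 values, the either-test rate would be about 10% for normal and 8–10% for skewed data (assumed correlation 0.6, 40 per arm).

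**5. Baseline adjustment, normal data.** With unit SD and correlation r, the variance is 2(1 − r) for change and 1 − r² for ANCOVA. Their ratio is (1 + r)/2, below 1 whenever r < 1. For 32 per arm and a 0.5 SD effect, the expected test statistic is the effect divided by the relevant SD, times √(32/2) = 4. Approximate power is Φ(statistic − 1.96).

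| r | Change | ANCOVA | Variance ratio |
|---|---|---|---|
| 0.5 | 0.5/1.000 × 4 = 2.00, 52% | 0.5/0.866 × 4 = 2.31, 64% | 0.75 |
| 0.6 | 0.5/0.894 × 4 = 2.24, 61% | 0.5/0.800 × 4 = 2.50, 71% | 0.80 |
| 0.8 | 0.5/0.632 × 4 = 3.16, 88% | 0.5/0.600 × 4 = 3.33, 92% | 0.90 |

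Simulation at r = 0.6, which uses the t distribution, gives slightly lower values: about 59% and 68%.

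**6. Skewed data.** Lognormal, log-SD 0.7, 32 per arm, 0.5 SD log-scale effect, correlation 0.6, tests on change. Power is about 57% for the gated test, 60% for a t-test on log change and 68–70% for ANCOVA on logs. The log scale accounts for about 3 points and baseline adjustment for about 8 to 10.

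**The case against.** **An analysis plan may rank the analyses.** An article commonly leaves the order of primary and sensitivity analyses, and any transformation, to a fuller document. That stands as far as silence goes. But the article does state the data-driven choice of test, the unconditional second model and the common threshold, and those statements do not fit together.

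**The harm is small.** A reader might infer that every skewed outcome will have two conflicting p-values for one hypothesis. The documents do not support that. The p-values differ, but they cross 0.05 in only about 3–22% of flagged trials. The nulls also differ: Mann-Whitney concerns a shift between distributions, the interaction a difference in mean change. The gated test alone holds its level, and inflation arises only if someone claims whichever test succeeds, which the article does not say will happen. This objection stands and limits the point.

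**The inputs are assumed.** Lognormal data with a multiplicative effect favour log-scale ANCOVA by construction, and markers such as HbA1c or HDL-cholesterol may not be skewed. This is fair. The gain from baseline adjustment, however, also appears with normal data.

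**The model is not fully described.** That the regression is a standard parametric one is an inference. A version forcing equal baseline means in the two arms would recover most of the ANCOVA gain, but the article does not describe one.

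**Time effects.** A reader might infer that regression to the mean will make all markers fall in both arms and that this will be read as benefit. Entry requires an "HbA1C value greater than 7"%, so the argument reaches HbA1c at most, and the article does not say whether the screening value is also the baseline value. Nothing in it says a time effect will count as efficacy.

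**Conclusion.** The point holds in limited form. The plan selects a test from the observed data, then runs a second treatment comparison on every outcome regardless, both at p < 0.05 and without precedence. With two visits and complete data, the second comparison duplicates the t-test on change for normal outcomes and is a rival answer for skewed ones. Mann-Whitney does not estimate the mean difference the plan says it compares.

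The inflation is modest. It is about 6 to 8% per skewed outcome, given assumed lognormal data and freedom to claim either result. The change reading gives 5.9–6.8%; the less likely week-10 reading starts at about 8% and reaches about 10%. The larger cost is power: about 59% without baseline adjustment against 68% with it, for a normal outcome at 32 per arm, a 0.5 SD effect and correlation 0.6. The gap narrows as the correlation rises. None of this invalidates the trial; it is a cheap improvement.

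**What to change.** Before unblinding:

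- Drop the Shapiro-Wilk gate.
- Name one primary analysis per outcome: the between-group comparison at week 10 adjusted for the baseline value (ANCOVA), with its estimate and 95% CI.
- Fix in advance a log transform for markers expected to be right-skewed, such as triglycerides, insulin and HOMA-IR. Report these as ratios of geometric means with 95% CI.
- Keep Mann-Whitney and the repeated-measures model as sensitivity analyses, and label them so.
- State that efficacy rests on the between-group contrast and that within-group time effects are descriptive.

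The cost is wording only, with no extra patients, visits or assays. The one drawback is that ratios of geometric means need a sentence of explanation for readers.

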## Ethical considerations

This clinical trial will be conducted after approval by the Ethics Committee of Tehran University of Medical Sciencesand after obtaining informed consent from the participants. Whenever a person is unable to continue supplementation, he/she will be excluded from the study.

## The limitations

One of the limitations of this study is the lack of cooperation of some patients who were replaced with other patients.

## Discussion

T2DM is a common chronic disease worldwide. Recently, herbal medicine has become more popular due to their beneficial effects [30]. Cardamom (*E. cardamomum*) is an expensive spice with an old history [31]. Today, cardamom is grown in India, Thailand, Guatemala, Ceylon and Malay Archipelago [26]. The main characteristics of cardamom include sweet odor, warm nature and mild strong taste that make it a popular spice [31]. Cardamom is rich in antioxidant compounds that cause elevation and activation of the antioxidant defense system [32].

To the best of our knowledge, this is the first randomized controlled trial that will determine the effect of cardamom on glycemic status, lipid profile, oxidative stress biomarkers, SIRT1 and irisin in T2DM. The selection of patients with T2DM is the main strength of the present study. The results of this trial will provide clinical evidence on the effectiveness and safety of cardamom supplementation in patients with T2DM.

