**Methods/design:**

Eighty overweight or obese patients with type 2 diabetes will be selected. They will be randomly assigned to receive 3 g/d green cardamom or placebo for 10 weeks. The socio demographic, physical activity and 24-h food recall questionnaires will be collected for each subject. Weight, height and waist circumference will be measured. Determination of blood glucose, lipid profile, and oxidative stress biomarkers including serum levels of total antioxidant capacity (TAC), malondialdehyde (MDA), and glutathione peroxidase (GPx) and superoxide dismutase (SOD) in red blood cells will be performed. The homeostasis model assessment-estimated insulin resistance **(**HOMA**-**IR**)** index and the quantitative insulin-sensitivity check index (QUICKI) will be calculated. Also, serum levels of irisin, and Sirtuin1 (SIRT1) will be measured.

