### Sample size:

The sample size was calculated using the following equation:$$ n=\frac{{\left({Z}_{1-\alpha /2}+{Z}_{1-\beta}\right)}^2\left({S}_1^2+{S}_2^2\right)}{{\left({\mu}_1-{\mu}_2\right)}^2} $$

A total of 40 diabetic patients were calculated in each group (cardamom and placebo groups) based on a significant mean difference of TAC [24], with 95% confidence level, 80% power and additional drop-out rate of 20%.

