### Patient safety

Patients will be monitored weekly during the study period and any occurrence of adverse events will be recorded.

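### The article promises evidence on safety, but names no safety outcome and drops from the study anyone who cannot continue the capsules, so follow-up of adverse events may be incomplete and selected for tolerance

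*Protocol article*

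**What the plan says.** The closing paragraph of the Discussion says: "The results of this trial will provide clinical evidence on the effectiveness and safety of cardamom supplementation in patients with T2DM". The abstract's own Discussion paragraph promises evidence on efficacy only, and the aims in the abstract and the Background concern glucose, lipids, oxidative stress and mechanism.

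- **Exposure.** From the abstract (Methods/design): "They will be randomly assigned to receive 3 g/d green cardamom or placebo for 10 weeks". Sample size gives 40 patients per group, including a 20% drop-out allowance, based on total antioxidant capacity (TAC).
- **Outcomes.** The primary list opens: "The primary outcomes of this clinical trial are the changes in HbA1C, FBS, insulin, lipid profile", and goes on to oxidative stress markers, SIRT1 and irisin. The secondary outcomes are weight, BMI and waist circumference. Neither list contains adverse events, tolerability or discontinuation.
- **Safety recording.** Under Patient safety: "Patients will be monitored weekly during the study period and any occurrence of adverse events will be recorded". Adherence adds a weekly telephone check.
- **Patients who stop.** Under Ethical considerations: "Whenever a person is unable to continue supplementation, he/she will be excluded from the study". Inclusion and exclusion criteria also removes patients who take under 90% of the intervention, and The limitations says that uncooperative patients were replaced.
- **Analysis.** Statistical analysis promises both intention-to-treat and per-protocol analysis of all outcome variables.

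**The concern.** Patients who cannot carry on with a supplement are the ones who tell most about its tolerability. A rule that takes them out of the study conflicts with a stated promise to inform on safety. If weekly contact stops when the capsules stop, events that begin, persist or worsen afterwards have no planned route into the data. The two arms may then be compared on patients who stayed because they tolerated what they took, and the number leaving may differ between arms.

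The intention-to-treat statement does not repair this. It covers outcome variables, and adverse events are not among them. The exclusion rule is also hard to square with that statement for the efficacy outcomes, since an intention-to-treat analysis needs the randomised patients who stopped.

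At stake is how a low adverse-event count would be read. Set beside the sentence in the Discussion, few or no events could pass for evidence of safety in type 2 diabetes, when the design can speak only to common, early events.

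**Working it through.** **Inputs from the article.** 40 patients per arm, 10 weeks, 20% drop-out (Sample size; abstract). The article gives no adverse-event rate, so the rates of 1%, 2%, 5% and 10% below are assumptions for illustration.

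**The plan's own figure.** The 40 per group cannot be rebuilt in full, because the article does not print the TAC difference and standard deviations; that is not a criticism here. The drop-out step is consistent: 32 / (1 − 0.20) = 40. So the plan allows for losing 40 − 32 = 8 patients per arm. No safety consideration enters the calculation.

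**1. Total exposure.** 40 × 10/52 = 7.7 patient-years on cardamom at most, before any replacements.

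**2. What zero events would exclude.** One-sided 95% upper limit for n patients with no event: 1 − 0.05^(1/n).
- n = 40: 1 − 0.05^(1/40) = 0.072, or 7.2%.
- n = 32 (only if completers alone are counted): 1 − 0.05^(1/32) = 0.089, or 8.9%.

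**3. Chance that an event never appears.** (1 − p)^n.

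| True rate p (assumed) | n = 40 | n = 32 |
|---|---|---|
| 1% | 67% | 72% |
| 2% | 45% | 52% |
| 5% | 13% | 19% |
| 10% | 1.5% | 3.4% |

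For example, 0.98^40 = 0.446.

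**4. Detectable difference between arms.** Normal approximation, two-sided 5% level, 40 per arm, p̄ the mean of the two rates:

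power = Φ{ [p1 − p0 − 1.96·√(2p̄(1 − p̄)/n)] / √([p1(1 − p1) + p0(1 − p0)]/n) }

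With p0 = 5% and p1 = 27.9%: p̄ = 0.1645; the square roots are 0.0829 and 0.0789; (0.229 − 1.96 × 0.0829)/0.0789 = 0.84; power = 0.80. In the same way, assumed placebo rates of 1% and 10% need cardamom rates of about 20% and 36%. Only very large differences would be detected.

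**5. The rules side by side.** Patient safety records any event during the study period. Ethical considerations ends study membership for anyone unable to continue. Read together, an event that causes a patient to stop falls within the recording, and an event after stopping does not. The under-90% rule points the same way for patients who cut down their intake. The article does not say whether events recorded before exclusion stay in the summary, nor which patients form its denominator.

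**The case against.** The strongest reply is that safety collection is planned: a separate section provides for weekly recording, in a double-blind trial with a placebo arm. Listing efficacy outcomes separately from adverse events is ordinary, and table layouts and analysis populations are commonly left to a fuller document. The sentence in the Discussion promises some evidence; it does not claim to establish safety or to cover rare or long-term harm. The zero-event limits apply to any trial of this size, and replacements may take the number exposed somewhat above 40.

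Most of this stands. The article cannot be faulted for failing to collect adverse events or for omitting tabulation detail, and the limits in the working only show the scale of what can be learnt.

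A reader might go further and infer that the exclusion rule deletes intolerant patients from the adverse-event count. The documents do not support that. Nothing says that events recorded before exclusion are discarded, and the event that led to stopping would normally have been recorded by then. For the same reason the 8.9% limit is conditional: it applies only if completers alone were counted, which is nowhere stated.

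What the reply does not meet is the rule itself. Exclusion from the study is stated in the article, and it leaves no provision for follow-up after stopping.

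**Conclusion.** The point holds as a mismatch between a claim, an outcome list and a stated exclusion rule. Loss of events after stopping, and a summary selected for tolerance, are risks that the text leaves open; they are not demonstrated biases. Their size cannot be computed from the article. The plan's allowance of 8 in 40 per arm is a guide to how many patients could be affected, if stopping accounts for the drop-out.

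Apart from that risk, the exposure supports a short-term tolerability statement and no more: zero events in 40 would leave rates up to 7.2% open, and an event with an assumed true rate of 2% would fail to appear with probability 45%. These figures assume 40 independent patients with complete recording.

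The sample size calculation is not affected. The same exclusion rule does need to be reconciled with the intention-to-treat statement for the efficacy outcomes.

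**What to change.** 1. **Ethical considerations.** Replace exclusion from the study by continued follow-up: patients who stop the capsules remain in the study for data collection. This concerns follow-up only, not the decision to stop. Bring the under-90% exclusion and the replacement of patients into line with the intention-to-treat statement.
2. **Adherence and Patient safety.** Continue the existing weekly calls to week 10 for patients who stop, and state that events recorded before stopping are kept.
3. **Secondary outcomes.** Add adverse events and discontinuations, reported by arm in all randomised patients who took at least one capsule.
4. **Discussion.** Limit the claim to 10-week tolerability, and give an upper confidence limit with any zero count.

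The cost is a few extra calls, one table and a slightly less favourable closing sentence. Items 1 to 3 carry most of the value; item 4 is mainly wording and reporting.
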